## Abstract

**Background:**

An individual education plan (IEP) is a key element in the support of the schooling of children with special educational needs or disabilities. The IEP process requires effective communication and strong partnership between families, school staff, and health care practitioners. However, these stakeholders often report their collaboration as limited and difficult to maintain, leading to difficulties in implementing and monitoring the child’s IEP.

**Objective:**

This paper aims to describe the study protocol used to evaluate a technological tool (CoEd application) aiming at fostering communication and collaboration between family, school, and health care in the context of inclusive education.

**Methods:**

This protocol describes a longitudinal, nonrandomized controlled trial, with baseline, 3 month, and 6-month follow-up assessments. The intervention consisted of using the web-based CoEd application for 3 months to 6 months. This application is composed of a child’s file in which stakeholders of the support team can share information about the child’s profile, skills, aids and adaptations, and daily events. The control group is asked to function as usual to support the child in inclusive settings. To be eligible, a support team must be composed of at least two stakeholders, including at least one of the parents. Additionally, the pupil had to be aged between 10 years and 16 years, enrolled in secondary school, be taught in mainstream settings, and have an established or ongoing diagnosis of autism spectrum disorder, attention-deficit/hyperactivity disorder, or intellectual disability (IQ<70). Primary outcome measures cover stakeholders’ relationships, self-efficacy, and attitudes toward inclusive education, while secondary outcome measures are related to stakeholders’ burden and quality of life, as well as children’s school well-being and quality of life. We plan to analyze data using ANCOVA to investigate pre-post and group effects, with a technological skills questionnaire as the covariate.

**Results:**

After screening for eligibility, 157 participants were recruited in 37 support teams, composed of at least one parent and one professional (school, health care). In September 2023, after the baseline assessment, the remaining 127 participants were allocated to the CoEd intervention (13 teams; n=82) or control condition (11 teams; n=45).

**Conclusions:**

We expect that the CoEd application will improve the quality of interpersonal relationships in children’s IEP teams (research question [RQ]1), will show benefits for the child (RQ2), and improve the well-being of the child and the stakeholders (RQ3). Thanks to the participatory design, we also expect that the CoEd application will elicit a good user experience (RQ4). The results from this study could have several implications for educational technology research, as it is the first to investigate the impacts of a technological tool on co-educational processes.

**International Registered Report Identifier (IRRID):**

DERR1-10.2196/63378

## Introduction

### Background

There is a growing body of literature on the benefits of using educational technologies to support children with special educational needs or disabilities (SEND) and, notably, those due to neurodevelopmental disorders (NDD; eg, [1-4]). Most of these technologies target students as their primary users, forgetting the social environment that has to work together to support the children in their educational project. This study aims to conduct a field study to assess the effectiveness of an interactive web application (namely, the CoEd application) for fostering collaboration between family, school, and health care practitioners.

In several countries, a key element in the support of the child’s schooling is the individual education plan (IEP), which defines their needs and gathers information on aids and adaptations that can be implemented to help them attain their full potential. IEP structures differ by country, but the core process emphasizes a robust partnership among families, school staff, and health care professionals, with regular meetings and a deep understanding of the child's profile and progress [5,6]. Effective communication between teachers and parents is universally recognized as a cornerstone of a child’s education [6,7]. The ability of parents to share pertinent information about their child’s disabilities, strengths, and weaknesses significantly enhances educators’ awareness and enables them to tailor their pedagogical approaches [8]. Furthermore, parental involvement in the educational process has far-reaching implications, encompassing the holistic development and well-being of children with SEND. It serves as the bedrock for fostering a culture of productive family-school collaboration and cultivating a supportive school environment [9,10]. For students grappling with complex disorders such as autism spectrum disorder (ASD), the synergy of collaboration between parents and educators paves the way for improved academic performance, smoother integration, and enhanced social adaptation [11]. In a broader context, collaboration between parents and educators emerges as a catalyst for positive outcomes, benefiting students across the spectrum of educational needs [12]. Despite all of this, studies on the IEP process consistently underscore the pronounced discord between stakeholders’ aspirations for effective teamwork and the actual communication and collaboration practices in place [12-17]. This paradox is particularly evident in the experiences of parents, teachers, and educators who frequently encounter obstacles ranging from resource constraints to training deficits, communication impediments, intercoordination challenges, and intricate administrative processes [12,18-22]. These challenges are not unique to inclusive education of children with NDD and extend to other areas such as patient care [23,24].

Within the continuum of collaborative practices in inclusive education, 3 progressive levels can be delineated: cooperation, coordination, and collaboration [25]. As elucidated by Larivée et al [26], elevation in the school-family-community collaboration level correlates with mutual recognition of expertise, bidirectional communication, shared responsibilities, and the spirit of reciprocity.

Several theoretical models of collaborative practices within the framework of IEPs have been proposed. These models may pivot around the child, exemplified by the “Whole School, Whole Community, Whole Child” model [27,28], or emphasize the dynamics of partnerships between stakeholders, as exemplified by the Sunshine model [29]. Other models are grounded in the objectives of IEPs, as demonstrated by polycentric approaches based on the child’s life project [30]. Additionally, some models embrace a multidimensional perspective typified by the Holistic School Care Coordination System Model [31,32].

The proliferation of these models underscores the pivotal role of educational systems in facilitating interactions between educators and families. This entails the provision of guidelines and recommendations for effective collaboration, alongside the allocation of critical resources encompassing time, physical infrastructure, and financial support [19,20]. Among the envisaged solutions, harnessing digital technologies emerges as a promising avenue to support continuous communication for efficient stakeholder collaboration [33,34].

### Prior Work

Maintaining communication and collaboration within the extended team for IEPs is challenging due to various communication channels like emails and phone calls. Despite digital advancements, tools often prioritize one-to-one communication over team-based sharing. Additionally, the lack of trackability in one-to-one exchanges hampers information flow within the team. To the best of our knowledge, very few digital tools are designed to help stakeholders with team-based information sharing, communication, and collaboration in the follow-up of the IEP and of the child’s schooling and development [35]. Many proposed devices in this field lack maturity, either due to an inadequate design that does not consider user needs, resulting in usability issues, or because participatory design methods were used without subsequent effectiveness studies conducted to standard methodological levels for producing evidence (for a review, see [35]). An example of that is illustrated by the CoEd application, which provides a web application with functionalities aiming at fostering information sharing, communication, and collaboration in IEP and with the support team [36]. Through participatory methods, the CoEd application was designed based on stakeholders’ needs and iterative design steps for eliciting good user experience, usability, and utility (see [36] for the design process).

### Aims

We propose to conduct a field study aiming to evaluate the impact of using the CoEd web application on 3 outcomes. First, we hypothesized that the CoEd application will improve communication and relationships between stakeholders (family, school, and health care practitioners), as well as their attitudes toward school inclusion, and increase each stakeholder’s perceived self-efficacy (research question [RQ]1). Second, we hypothesized a beneficial effect of using CoEd on the child in terms of behavioral or academic functioning (RQ2). Third, we expect that using CoEd results in a better quality of life for both the stakeholders and the children (RQ3). Finally, as it is crucial when evaluating technology to verify that it is both effective and usable [37], we added measures related to the user experience of participants. Thanks to the participatory design, we expected that the CoEd application will elicit a good user experience (RQ4).

The paper follows the SPIRIT (Standard Protocol Items: Recommendations for Interventional Trials) guidelines for reporting study protocols [38]. The SPIRIT checklist for this paper is provided in Multimedia Appendix 1.

## Methods

### Ethical Considerations

The ethics committee (Comité Opérationnel d'Évaluation des Risques Légaux et Éthiques [COERLE]) of the French National Institute of Informatics and Mathematics (Inria) approved the study protocol (application number 2022-08).

As the study protocol implies the management of health-related data, the CoEd app is hosted and managed on a secured server at Inria as if CoEd’s data are medical data, in respect of the General Data Protection Regulation (GDPR). Additionally, the study protocol and data management processes were approved by the National Commission of Informatics and Liberty and by the Inria Security Homologation committee (application number 13953). All participants were informed about the study and gave written informed consent.

### Study Overview

We designed a longitudinal, nonrandomized controlled trial to evaluate the impact of the CoEd application developed by our team [36]. We enrolled teams monitoring the school or social inclusion of secondary school pupils with NDD (between 10 years and 16 years old). These teams were recruited throughout France via email communication with schools, school districts, special education advisors, academic inspectors specializing in Special Education, and associations supporting families of children with NDD. Field partners of the project, namely the Nouvelle-Aquitaine academy, Autism Resources Center, and Association pour la Réadaptation et l'Intégration, were also engaged in the recruitment process and encouraged participation in their networks. We also put out calls for participants on digital social networks. Parents, teachers, and health care professionals were asked to complete a questionnaire to check the inclusion criteria. When the participant and child were eligible, all the members of the follow-up team were contacted, and the study was presented to them. Once participation was confirmed, individual participants received a consent form. They were given a week to return the completed form, with researchers available to address any questions during this period.

Whether they were in the control or experimental condition, they had to complete a baseline assessment and a 3-month follow-up assessment, and if they were willing to continue participating, they would complete a 6-month follow-up assessment (Figure 1).

**Figure 1 figure1:**
[figure not shown]
Timeline of the field study according to the group conditions and the number of school terms (3 months for each term) for study participation.

### Eligibility Criteria

To participate, a support team had to consist of at least two stakeholders, including at least one of the parents. Additionally, the pupil had to be aged between 10 years and 16 years, enrolled in secondary school, be taught in mainstream settings, and have a diagnosis of ASD, attention-deficit/hyperactivity disorder, or intellectual disability (IQ<70). The pupil needed either an established diagnosis or to be undergoing a multidisciplinary intervention for diagnosis.

### Allocation and Blinding

In this quasi-experimental trial, the group allocation was not randomized. Group allocation was carried out as participants were recruited according to eligibility criteria, taking care to balance groups in terms of team size. A nonrandomized procedure was chosen because we recruited participants as volunteers arose who had a complete team. As the control group did not use the CoEd application and functioned as usual whereas the experimental group was asked to use the CoEd application and needed secure access to the web-based application, it was not possible to conduct a double-blind study.

### Outcome Measures

#### Selection of Outcome Measures

Outcome measures were chosen from the researchers’ hypotheses and participatory decision-making. In 2 focus groups, parents, teachers, and health care professionals discussed the CoEd application’s potential impact and evaluation criteria (Multimedia Appendix 2). Participants reviewed preselected indicators and suggested new measures, especially concerning quality of life and caregiver burden, for the field study. As a result, the primary outcomes include 3 main dimensions (ie, stakeholders’ relationships, perceived individual efficacy, and attitudes toward school inclusion). To this end, parents, teachers, and health care professionals completed a series of common or specific questionnaires (Table 1). The secondary outcomes include measures for stakeholders (burden and quality of life) and for the children (quality of life, school well-being, and school inclusion perception; Table 1). Additionally, a measurement of technology experience that covers technology skills and CoEd experience was included for the intervention group (Table 1). Although some questionnaires had a validated French version, others did not. In the latter case, as we are French native speakers, we translated them in collaboration with native English speakers. The scales used are presented in Table 1.

**Table 1 table1:** Description of the assessment batteries to address the targeted (primary and secondary) outcomes and technology experience of participants.

Outcomes, dimension, and subdimension				Questionnaire		Respondent						
						Child		Parent		Teacher		Professionals
**Primary outcomes (stakeholders)**												
	**Relationship**											
		Parent-teacher	Parent-Teacher Relationship Scale II^a^		—^b^		X		X		—	
		Therapeutic or interprofessional	Helping Alliance Questionnaire		—		X		X		X	
	**Perceived educational efficacy**											
		Self-efficacy	Basic Psychological Need: Satisfaction and Frustration scale		—		X		X		X	
		Achievement of educational goals	Goal Attainment Scale		—		X		X		X	
	**Attitudes toward school inclusion**											
		Teachers	Multidimensional Attitudes Towards Inclusive Education Scale		—		—		X		—	
		Parents	Attitudes Toward Inclusion/Mainstream^a^		—		X		—		—	
**Secondary outcomes (stakeholders)**												
	**Burden**											
		Family burden	Caregiver Strain Questionnaire		—		X		—		—	
		Adult burden	Zarit Inventory Short Form		—		—		X		X	
		Burnout	Maslach Burn-out Inventory^a^		—		X		X		X	
	**Quality of life**											
		Adult	WHOQOL-Bref		—		X		X		X	
		Family	Beach Center Family Quality of Life (FQOL)		—		X		—		—	
**Secondary outcomes (children)**												
	**School life**											
		Child’s quality of life	Pediatric Quality of Life Inventory (PedsQL)		X		X		—		—	
		School well-being	Multidimensional Students' Life Satisfaction Scale (MSLSS)		X		—		—		—	
		School inclusion	Individual school perception		X		—		—		—	
**Technology experience^c^**												
	**Technology skills**											
		Computer skills	Computer Usage Questionnaire		—		X		X		X	
	**CoEd** **application experience**											
		Subjective user experience	User Experience Questionnaire, short version and Technology-based Experience of Need Satisfaction (TENS)^a^		—		X		X		X	
		Objective user experience	The uses and usages of the CoEd application are quantified with the following indicators across periods of 3 months or 6 months: (1) number of times the application is opened and (2) number of exchanged posts		—		X		X		X	

^a^Translated in French by the authors.

^b^Not applicable.

^c^Intervention group only.

#### Primary Outcomes

##### Perception of Stakeholders’ Relationships

Parents and teachers completed the Parent-Teacher Relationship Scale [39], which consists of a 24-item questionnaire measured on a 5-point Likert scale (1=strongly disagree to 5=strongly agree) assessing the 2 dimensions joining and communication-to-other, including their feeling of affiliation and support; the dependability and availability of both parties; shared expectations; and beliefs about the child and each other, their communication, and their sharing of information and emotions. To assess the relationship with medical-social professionals, the Helping Alliance Questionnaire [40] was completed by parents, teachers, and health care practitioners. The Helping Alliance Questionnaire initially evaluated the therapeutic alliance through the 2 dimensions perceived helpfulness and collaboration, but it was adapted to the purpose of the study. Two versions were used: a 13-item parent form and an 11-item professional form, both using a 6-point Likert scale (1=totally disagree to 5=totally agree).

##### Perceived Individual Efficacy

The feeling of self-determination was measured using the French version of the Basic Psychological Need Satisfaction and Frustration Scale [41], which assesses satisfaction and frustration with the 3 basic psychological needs: competence, affiliation, and autonomy. This 24-item scale using a 5-point Likert scale (1=Completely False to 5=Completely True) provides a proxy of general individual efficacy. A version of the Goal Attainment Scale [42] adapted by our team was proposed. Initially, parents and professionals were asked to independently specify 2 to 5 school, social, or behavioral goals for the young individual, along with their current level, desired level, difficulty, and importance. At the end of the experimentation, the goal was recalled, and the adults were asked to assess the level of goal attainment. This adapted version of the Goal Attainment Scale provides a probe of (individual) educational efficacy.

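### The primary Goal Attainment Scale scores adult-rated attainment of goals set for the child, so it bears on RQ2 and should not be read as evidence of increased stakeholder efficacy under RQ1

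*Protocol article*

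**What the plan says.** Table 1 of the protocol article places the Goal Attainment Scale among the primary outcomes for stakeholders. It sits in the dimension on perceived educational efficacy, under the subdimension "Achievement of educational goals". Parents, teachers and professionals complete it; the child does not.

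The section Perceived Individual Efficacy describes the procedure. At the start, "parents and professionals were asked to independently specify 2 to 5 school, social, or behavioral goals for the young individual", with a current level, a desired level, a difficulty and an importance for each goal. At the end, "the goal was recalled, and the adults were asked to assess the level of goal attainment". The section then interprets the score: "This adapted version of the Goal Attainment Scale provides a probe of (individual) educational efficacy".

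The Aims tie RQ1, on this point, to each stakeholder's "perceived self-efficacy (research question [RQ]1"). RQ2 concerns the child: "we hypothesized a beneficial effect of using CoEd on the child in terms of behavioral or academic functioning (RQ2"). Planned Statistical Analyses maps the primary outcomes to RQ1 and the secondary outcomes to RQ2 and RQ3.

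**The concern.** The score is interpreted as a property of the adult, but what is rated is whether goals set for the child were reached. The two can move separately. A child may reach a goal through maturation or other support while no adult feels or becomes more capable. An adult may grow in efficacy while a hard goal stays unmet.

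What is at stake is the RQ1 conclusion. With the mapping as written, a higher attainment score in the CoEd group counts toward the claim that the application strengthens stakeholders' efficacy, although it shows adult-reported progress of the child. The same mapping also takes away from RQ2 the measure whose content lies closest to its hypothesis.

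**Working it through.** No arithmetic decides this point. The check sets the article's statements side by side.

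1. **Object of the goals.** They are school, social or behavioral goals for the young person (Perceived Individual Efficacy).
2. **What is scored at the end.** The adults rate the level of attainment of those goals (same section). No described step asks about the adult's confidence, capability or contribution.
3. **Construct assigned.** The score is said to probe individual educational efficacy (same section), and Table 1 files it under perceived educational efficacy.
4. **Research question assigned.** Primary outcomes go to RQ1 (Planned Statistical Analyses). The only efficacy hypothesis in RQ1 is a rise in perceived self-efficacy (Aims).
5. **Research question matched by content.** RQ2 is about the child's behavioral or academic functioning (Aims), which is close to the content in step 1. Strengths and Limitations also speaks of the achievement of academic and social objectives as a gain for each child.
6. **What RQ2 has otherwise.** The child outcomes in Table 1 are quality of life, well-being at school and perceived school inclusion. None is dedicated to behavioral or academic functioning. The nearest are the functioning subscales of the PedsQL (Child's Quality of Life).

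Steps 1, 2 and 5 point to the child and RQ2. Steps 3 and 4 point to the adult and RQ1. Nothing described in the procedure bridges them.

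**Extent.** Table 1 lists six primary instruments: two for relationships, two for efficacy and two for attitudes (2 + 2 + 2 = 6). The Goal Attainment Scale is 1 of the 2 efficacy instruments and 1 of the 6. The other efficacy instrument, the Basic Psychological Need Satisfaction and Frustration Scale, asks adults about themselves and is the one Table 1 lists for self-efficacy.

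**Number of ratings.** Attainment can be rated only at follow-up. The Results section reports 89 participants remaining at 3 months and 67 at 6 months, so these are upper bounds on the number of raters. The article does not say whether these counts include children.

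**Structure of the data.** Several adults in a team rate goals for the same child, but each set goals independently. The scores are therefore correlated within a child without being repeat ratings of one quantity. The pooled analysis in Planned Statistical Analyses sets team membership aside.

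**The case against.** The strongest defence is that the article does not call goal attainment self-efficacy. Table 1 separates a self-efficacy subdimension from the one on educational goals, and the text separates a proxy of general efficacy from a probe of educational efficacy. The adults choose the goals, and the Discussion, under RQ1, speaks of stakeholders' capability to reach the goals they hold as educators. On this view, attaining goals one has set as an educator is a defensible, openly labelled index of educational efficacy. The item wording of the adapted scale and the focus-group appendix, which might support it, are not shown.

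Part of this stands. The distinction in Table 1 is real, and the intended reading is clear. But the goals elicited are for the child, the described rating does not isolate the adult's part in reaching them, and RQ1 states no efficacy hypothesis other than perceived self-efficacy.

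Several stronger readings are tempting and are not supported:

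- **That the scale scores the child's own goals, or the child alone.** Adults set the goals, and the score is an adult's perception. Blinding was not possible, so it mixes change in the child with the rater's view.
- **That about 24 children (13 + 11 teams) are being counted as 127 adult ratings.** The figure of 127 is the count after baseline, before attainment could be rated. The article does not state that all are adults, and one pupil per team is an inference from the eligibility criteria.
- **That a null result would be read as no efficacy gain.** The dimension has a second instrument, and no rule lets this scale decide RQ1 alone.
- **That the scale should be demoted to a secondary outcome.** Moving a declared primary outcome after data collection would raise a concern about outcome switching.

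Maturation or other support can also occur in the control group, which is measured on the same schedule. That gives some protection, although without randomization such influences cannot be assumed balanced. It does not alter what the score measures: even a true group difference in attainment would be a difference in rated progress of the child.

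**Conclusion.** The concern holds as a mismatch between the content of the score and the research question it is made to serve. It affects one of two efficacy instruments and one of six primary instruments; it does not undermine the whole efficacy dimension. No numerical bias can be given, because the article reports nothing on how attainment ratings relate to adult efficacy.

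The conclusion assumes that the published description of the adapted scale is complete in one respect: that no item asks adults about their own contribution or capability. If the full instrument contains such items, they could support an efficacy reading and should be reported separately. The case for modelling clustering rests on several adults rating goals for the same child, which the team structure implies.

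**What to change.** Keep the scale's declared primary status and change its label, use and model:

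- In Table 1 and Perceived Individual Efficacy, describe it as adult-rated attainment of goals set for the child.
- Use it as evidence for RQ2, and amend the mapping of outcomes to research questions in Planned Statistical Analyses accordingly.
- Do not use it as evidence of increased stakeholder self-efficacy. Rest that RQ1 claim on the Basic Psychological Need Satisfaction and Frustration Scale, noting that the article itself calls that scale a proxy.
- Analyse attainment with a random effect for child/team and a term for rater role (parent, teacher, professional). A simple child-level mean is less suitable, because raters set different goals.
- Date the change and disclose it as a change of interpretation. The article reports that data collection ended in June 2024 and that data cleaning and analysis began in March 2025.

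No new data are needed. The cost is that the RQ1 efficacy claim loses one of its two instruments, and intervals for goal attainment may widen once clustering is modelled. The article gives neither the number of teams at follow-up nor a within-team correlation, so the widening cannot be computed from it.
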